### Participant timeline

Figure 1 outlines participant timeline and Table 2 illustrates the study assessment schedule.

**Fig. 1 Fig1:**
[figure not shown]
Participant timeline

**Table 2 Tab2:** Study assessment schedule

Study assessment schedule	Baseline	Immediately post intervention	3–6 months post intervention
Demographic and clinical characteristics	✓	✓	✓
Falls questionnaire	✓	✓	✓
Parkinson’s KinetiGraph recording^a^	✓	✓	✓
Validated questionnaires^b^	✓	✓	✓
Health Care Resource Utilisation Form	✓	✓	✓
Compliance		✓	

^**a**^Performed within ≤ 30 days prior to baseline and post intervention. ^b^The following scales will be completed at week 6: MDS-UPDRS Part II and PDQ-8 (participants will be sent these by post/electronically to complete at home and return to the study team)

### Sample size

Given that no previous studies explored the effect of ballet dancing on the symptoms of PD, sample size calculation is based on detecting a significant difference between intervention and the control group in the mean changes from baseline to follow-up in the primary outcome (MDS-NMS). To date, no clinical trials have yet utilised MDS-NMS as an outcome measure due to its novelty. As such, our estimation of the sample size is based on detecting a medium effect size (Cohen’s d 0.5) with 80% power and 5% significance, resulting in the total of 144 participants. Given that the randomisation ratio is 2:1, the intervention group is expected to include 96 participants and the control group 48 participants. Allowing a 10% attrition rate for the final analysis, the total number of participants in the study will be 160. The study is powered as a superiority study at immediate follow-up.

### Recruitment

Participants will be recruited mainly through the regional, national, and tertiary Movement Disorders outpatient clinics at the Parkinson’s Foundation Centre of Excellence, King’s College Hospital NHS Foundation Trust, London, United Kingdom. The study will be advertised via the South London Clinical Research Network, Parkinson’s UK Centre of Excellence Network, King’s Parkinson’s website (www.parkinsons-london.co.uk) and the corresponding social media, as well as the English National Ballet network. Recruitment strategies are outlined in Fig. 2. Recruitment period was originally planned to last for 12 months, but due to Covid-19 restrictions, this has been extended to 18 months. Participation eligibility will be determined at screening, with a subsequent assessment of motor advancement to ensure appropriate group allocation (mild, moderate or severe motor PD) (Table 3).

**Fig. 2 Fig2:**

Recruitment strategies

**Table 3 Tab3:** Stratification of study participants

Group 1: mild	Hoehn and Yahr stages I and II
Group 2: moderate	Hoehn and Yahr stage III
Group 3: severe	Hoehn and Yahr stages IV and V

## Assignment of interventions: allocation

### Sequence generation

Following motor advancement stratification, participants will be randomly assigned to one of the two arms (intervention or control group) using an in-house, electronic randomisation system provided by King’s Health Partners, an independent body providing support for studies conducted at King’s College Hospital.

### Concealment mechanism

After informed consent and baseline data collection, participants will be randomly divided into one of the two arms at a ratio of 2:1, intervention and control group specifically. Participant allocations will be kept concealed with an unblinded study coordinator, who will contact all participants will allocations prior to commencement of the intervention. Study raters will remain blinded.

### Implementation

All procedures will be implemented in accordance with the protocol approved by the NIHR Research Ethics Committee. A local Research and Development department will ensure appropriate protocol implementation and monitoring. Additionally, the Research Ethics Committee requires an annual progress report to ensure appropriate implementation of the study protocol and safety oversight.

## Assignment of interventions: blinding

### Who will be blinded

Study personnel will consist of blinded raters and unblinded coordinators who will be in communication with the ENB coordinators to ensure that the right participants are enrolled onto the appropriate sessions (intervention and social session as opposed to social session only). Medical oversight will be provided by unblinded neurologist. Data analyst will remain blinded.

### Procedure for unblinding if needed

N/A due to the fact that there is an unblinded medical oversight.

## Data collection and management

### Plans for assessment and collection of outcomes

Prior to any data collection, all study personnel will be trained on the relevant standard operating procedures implemented locally at study sites. All personnel will also complete GCP training and, where applicable, blinded raters will be trained on the use of study assessments, including the MDS-UPDRS and MDS-NMS certifications. Blinded raters will be kept consistent across study visits to minimise inter-rater variability. Where possible, electronic data collection will be enabled to minimise participant burden during the study visits on site. For patient-completed outcomes, all participants will be sent a participant-reported case report forms to complete at home on the day of the in-clinic study visits. An independent data monitoring will be utilised to ensure transparency and traceability. All data will be entered onto an electronic data capture designed and maintained by the Clinical Trials Unit at King’s Health Partners. On study completion and upon query resolution, the study database will be locked and validated for analysis.

### Plans to promote participant retention and complete follow-up

There are no specific plans to promote participant retention.

### Data management

All data will be managed by the research team and monitored by an independent coordinator. Study data will be entered onto electronic database and checked for validity and accuracy. Upon all query resolution, the database will be locked for analysis. Any changes to the locked database will be agreed upon by the trial statistician, data manager and the chief investigator.

### Confidentiality

Study team will have access to confidential information including medical notes for study participants. Once enrolled, all participants will be assigned a study identifier (ID) and all case report forms will only bear participant study ID. No personal data will be shared with individuals outside of the study team. Upon trial completion, all participant data will be fully anonymised before statistical analyses. All procedures pertaining to anonymisation have been approved by the Research Ethics Committee.

### Plans for collection, laboratory evaluation and storage of biological specimens for genetic or molecular analysis in this trial/future use

N/A. No biological samples will be collected.

## Statistical methods

### Statistical methods for primary and secondary outcomes

The first stage of analyses will be a descriptive model of the data to assess completeness of data and the integrity of the data collection system. Participant and centre characteristics and demographics will be summarised at baseline. Clinical characteristics that have been measured repeatedly will be summarised at baseline and at the post intervention follow-up assessments. In addition, patterns of missing data will be described.

The primary clinical outcome will be analysed using linear mixed effects models, to model the difference in means in total score of MDS-NMS between the two arms (Ballet vs Standard therapy) at immediate post intervention follow up. Linear mixed effects models will be adjusted for baseline total score of MDS-NMS and the severity of PD (HY staging). A two-level hierarchical model will be employed when all time points will be included as repeated measures in the model (post intervention and 6 months) to improve power and take into account clustering of the observation at patient level. These models utilise maximum likelihood estimation and thus allow for missing outcome data under the missing at random (MAR) assumption. Associations between post-randomisation variables and missingness will be dealt with by multiple imputation (MI), again under the MAR assumption. Departures from this assumption will be assessed with a sensitivity analysis. Secondary outcomes will be assessed with a similar methodology for the primary outcomes, using generalized linear mixed models depending on the type of outcome (normal, binary, count). All the questionnaires to be used would have validated methods of scoring, and the scores will be analysed as described.

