### Intervention description

The intervention programme will be delivered within a dance studio and led by four specialist dance artists and musicians trained by ENB, with support of assistants. Participants will engage in weekly classes, incorporating live music, dance, rhythm and voice. Artistic content is inspired by ENB’s classical and contemporary works and will provide a framework for participants to explore narrative, characters, themes, concepts and music. A seated or standing warm-up will involve stretches of the torso in all directions, a focus on breathing and a balanced posture, followed by emphasised movement of the lower body and rhythmic exercises to challenge coordination. Musicians and dance artists will work together to introduce various vocal warm-ups inspired by the artistic theme to introduce another layer of expression and intention. The class will develop from the barre to the centre with travelling dance phrases either with a partner or in formation, followed by structured improvisation tasks and the learning and development of repertoire dance phrases. All dance material is adapted as necessary for each individual to participate fully. Each dance session will comprise one hour and fifteen minutes of the activity, followed by “tea and biscuits” social time and refreshments for up to one hour. The total duration of the intervention will be 12 weeks for both the active and the control groups. The intervention will be delivered by the same dance artists and supporting staff across the three groups.

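### Dance is taught in shared classes, but the model stops at patient level and the sample size assumes independent participants; if outcomes correlate within class, the primary interval is too narrow

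*Protocol article*

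**What the plan says.** **Delivery.** Under Intervention description, the Protocol article states: "Participants will engage in weekly classes, incorporating live music, dance, rhythm and voice". The same section describes work in pairs and in formation, a social hour after each session and a 12-week course. It adds: "The intervention will be delivered by the same dance artists and supporting staff across the three groups". Controls have standard care and the social session only, which they may join remotely or in person.

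**Model.** Under Statistical methods for primary and secondary outcomes, the primary analysis is a linear mixed model adjusted for baseline MDS-NMS total and Hoehn and Yahr (HY) stage. The repeated-measures version is described as two-level, "to improve power and take into account clustering of the observation at patient level". The levels are therefore visit and patient. Because the article names them, leaving out the class is a stated choice and not a detail deferred to the analysis plan.

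**Sample size.** The section is based on "detecting a medium effect size (Cohen’s d 0.5) with 80% power and 5% significance, resulting in the total of 144 participants". It continues: "Given that the randomisation ratio is 2:1, the intervention group is expected to include 96 participants and the control group 48 participants". The inflation to 160 is for attrition only: "Allowing a 10% attrition rate for the final analysis, the total number of participants in the study will be 160". No ICC, class size or design effect appears.

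**The concern.** People who dance together for 12 weeks share a room, partners, an atmosphere and a pattern of attendance, so their outcomes may be more alike than those of dancers in different classes. Controls attend no class. This is a partially nested design: one arm is clustered by class and the other is not, or much less so.

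A model without a class level treats 96 dancers as 96 independent pieces of information. With any positive within-class correlation, the standard error of the arm difference is understated. The primary superiority test then rejects a true null more often than 5% of the time, and a model that respects the clustering has less power than the independent-participant formula suggests. What is at stake is the credibility of the primary interval.

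**Working it through.** **1. Reproduce the plan's figure.** Inputs from Sample size: d = 0.5, 5% significance (two-sided reproduces the figure; a one-sided test would give 114), 80% power, 2:1 allocation.

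- SE0 = √(1/96 + 1/48) = 0.1768 in SD units.
- Power = Φ(0.5/0.1768 − 1.96) = 80.7%, or 80.2% by noncentral t.
- 144/0.90 = 160.

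The plan's numbers are right for independent participants and leave no room for a design effect.

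**2. Add class clustering in the dance arm only.** Class size m and ICC are assumptions: m from 8 to 16, ICC from 0.01 to 0.05.

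- Design effect: DE = 1 + (m − 1) × ICC.
- SE = √(DE/96 + 1/48).
- Power = Φ(0.5/SE − 1.96).
- Type I error if class is ignored = 2[1 − Φ(1.977 × SE0/SE)], where 1.977 is the t critical value on 142 df.

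Example, m = 16 and ICC 0.05: DE = 1 + 15 × 0.05 = 1.75; SE = √(1.75/96 + 1/48) = 0.1976; ratio 0.1976/0.1768 = 1.118; power = Φ(2.530 − 1.96) = 71.6%; type I error = 2[1 − Φ(1.977/1.118)] = 7.7%.

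**3. Allow for the planned baseline adjustment.** Take d as standardised by the SD of change, since the section powers a difference in mean changes. With baseline to follow-up correlation r, adjustment multiplies the variance by (1 + r)/2. This is shown for assumed r of 0.5 and 0.7, with the same ICC for the adjusted outcome.

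| m | ICC | SE/SE0 | Naive type I | Power, unadjusted change | Power, r = 0.5 | Power, r = 0.7 |
|---|---|---|---|---|---|---|
| 8 | 0.01 | 1.012 | 5.1% | 79.8% | 89.8% | 85.8% |
| 8 | 0.05 | 1.057 | 6.1% | 76.3% | 87.1% | 82.7% |
| 12 | 0.01 | 1.018 | 5.2% | 79.3% | 89.4% | 85.4% |
| 12 | 0.05 | 1.088 | 6.9% | 73.9% | 85.1% | 80.5% |
| 16 | 0.01 | 1.025 | 5.4% | 78.8% | 89.0% | 84.9% |
| 16 | 0.05 | 1.118 | 7.7% | 71.6% | 83.2% | 78.3% |

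With 1.96 in place of 1.977, the type I column runs from 5.3% to 8.0%.

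**4. Few classes.** The power columns use the normal approximation. With k = 96/m classes and Satterthwaite df = SE⁴ / [(DE/96)²/(k − 1) + (1/48)²/47], power at ICC 0.05 for m = 8, 12 and 16 is:

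- unadjusted change: 74.5%, 71.0% and 67.3%;
- r = 0.5: 85.6%, 82.7% and 79.4%;
- r = 0.7: 81.1%, 77.9% and 74.3%.

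**5. What adjustment does not do.** The factor (1 + r)/2 multiplies the naive and the true variance alike, so SE/SE0 and the type I column do not change. Any ICC left after adjustment still distorts the test.

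**The case against.** The best case against the point is that its size rests wholly on assumed inputs. At ICC 0.01 with classes of 8 to 16, power is within 2 points of 80% and type I error is barely above 5%; at ICC 0 nothing is lost. The sample size also takes no credit for baseline adjustment, and with it power at ICC 0.05 stays near or above 80% over most of the range. The same artists teach throughout, which limits correlation through the teacher. If classes follow HY strata, the HY term absorbs part of the difference between classes. Calendar effects touch both arms and largely cancel where dancers and controls of the same period are compared, and the social hour is open to controls too.

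Most of this stands, and it limits the power argument in particular. It does not remove the validity argument. A single teaching team leaves peer and attendance effects in place, the HY term is common to both arms while class effects arise mainly in one, and baseline adjustment leaves the type I error where it was.

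A reader might also take the three groups under Intervention description to mean three classes of 32, for which ICC 0.05 would give 63% unadjusted power and 10.8% type I error. The article does not support that. The phrase most naturally refers to the mild, moderate and severe groups of Table 3, and recruitment from March 2022 to an expected December 2023 with a 12-week course points to repeated runs.

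**Conclusion.** The point holds in conditional form. The class level is absent from both the stated model and the sample size. If within-class correlation is above zero, the primary analysis as written gives too narrow an interval and a type I error above 5%. For assumed ICC 0.01 to 0.05 and classes of 8 to 16, the standard error is understated by a factor of 1.01 to 1.12, type I error is about 5.1% to 7.7%, and unadjusted power is about 80% to 72%.

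A reader might infer that the standard errors are wrong as a matter of fact and that the trial misses its 80% power. The document does not establish either. It gives no class size and no ICC, and baseline adjustment could put power at about 78% to 90% (r of 0.5 to 0.7, normal approximation, lower with few classes). The effect lies somewhere between negligible and material. Severity: should fix.

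**What to change.** 1. Record a class identifier for every dancer, marking who was taught together.
2. Add to the primary model a class random effect active in the dance arm only, with Satterthwaite or Kenward-Roger degrees of freedom.
3. If there are too few classes to estimate that variance, report a sensitivity analysis with the ICC fixed at values from 0.01 to 0.05.
4. In Sample size, say that 80% holds for independent participants only, and show power over that ICC range with the assumed class size and baseline adjustment.

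The cost is one variable and some wording. Recruitment was still open when the article was written, so this could be settled before database lock. No extra patients are needed. The downside is a slightly wider interval and a less favourable stated power.

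### The linear mixed models are stated as maximum likelihood; restricted maximum likelihood with a small-sample degrees-of-freedom method has the same MAR property and removes a small anti-conservative bias

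*Protocol article*

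**What the plan says.** All of the following is in the protocol article.

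- **Primary model** (Statistical methods for primary and secondary outcomes): "The primary clinical outcome will be analysed using linear mixed effects models, to model the difference in means in total score of MDS-NMS", with the contrast taken between arms immediately after the intervention.
- **Covariates** (same section): "Linear mixed effects models will be adjusted for baseline total score of MDS-NMS and the severity of PD (HY staging").
- **Repeated measures** (same section): "A two-level hierarchical model will be employed when all time points will be included as repeated measures in the model (post intervention and 6 months").
- **Estimation and missing data** (same section): "These models utilise maximum likelihood estimation and thus allow for missing outcome data under the missing at random (MAR) assumption". No degrees-of-freedom method or reference distribution is given.
- **Secondary outcomes** (same section): "Secondary outcomes will be assessed with a similar methodology for the primary outcomes". The model family is then chosen by outcome type, so that binary and count scores get a generalised mixed model.
- **Sample size**: "detecting a medium effect size (Cohen’s d 0.5) with 80% power and 5% significance, resulting in the total of 144 participants". The split is stated as follows: "Given that the randomisation ratio is 2:1, the intervention group is expected to include 96 participants and the control group 48 participants".

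**The concern.** The sentence on estimation gives MAR validity as what follows from using maximum likelihood. REML is also likelihood-based and is valid under the same assumption, so nothing is gained on missing data by choosing ML.

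Something small is lost. ML estimates the variance components as if the mean parameters were known. The downward bias passes into the standard error of the treatment effect, so intervals are a little too narrow and the test is a little too liberal. The error runs in one direction, towards declaring an effect. It grows as the number of contributors falls relative to the number of mean parameters. That is why carrying the method over to the secondary outcomes deserves a look as well as the primary analysis.

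**Working it through.** **1. The plan's own figure.** With d = 0.5, 80% power, two-sided 5% (sidedness is assumed) and 2:1 allocation, the control group needs (1.960 + 0.842)² × (1 + 1/2) / 0.5² = 47.1, rounded up to 48. The intervention group is then 96 and the total 144. Allowing 10% attrition, 144 / 0.90 = 160. Both stated figures reproduce, and power at 96/48 is 80.2% by t-test.

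**2. Number of mean parameters, p (assumption).** The article does not say how Hoehn and Yahr (HY) enters the model. For a single follow-up:

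- Intercept, arm, baseline and a linear HY term: p = 4.
- HY in the three groups of Table 3: p = 5.
- HY as five categories: p = 7.

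With both follow-ups, HY in three groups, and time and arm-by-time terms, p is also 7.

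**3. Single follow-up, closed form.** For a Gaussian linear model, SE(ML) / SE(REML) = √((N − p) / N). The true rejection rate of a nominal 5% test is 2 × P(T > c × ratio), where T has N − p degrees of freedom and c is either the t quantile or 1.960.

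| N | p | SE ratio | ML, t reference | ML, normal reference | REML, normal reference |
|---|---|---|---|---|---|
| 144 | 4 | 0.986 | 5.3% | 5.5% | 5.2% |
| 144 | 5 | 0.983 | 5.4% | 5.6% | 5.2% |
| 144 | 7 | 0.975 | 5.6% | 5.8% | 5.2% |
| 60 (assumed) | 4 | 0.966 | 5.8% | 6.3% | 5.5% |
| 60 (assumed) | 7 | 0.940 | 6.5% | 7.1% | 5.5% |

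REML with a t reference is exactly 5% in this setting. At N = 144, coverage of the 95% interval under ML is therefore 94.2–94.7%.

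**4. Two follow-ups.** Assume a within-patient correlation of 0.6 and complete data. The effect at the first follow-up then draws (1 + 0.6)/2 = 0.8 of its variance from patient means and (1 − 0.6)/2 = 0.2 from within-patient differences. Patient means carry five mean parameters (intercept, arm, baseline, two for HY) and differences carry two (time, arm-by-time). The variance ratio is approximately

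0.8 × 139/144 + 0.2 × 142/144 = 0.772 + 0.197 = 0.969,

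so the SE ratio is √0.969 = 0.985. At an assumed 60 contributors it is √(0.8 × 55/60 + 0.2 × 58/60) = √0.927 = 0.963.

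**5. Simulation of the same repeated-measures model** (correlation 0.6, three HY groups).

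| Contributors | Runs | SE ratio | ML, normal reference | REML, Satterthwaite t |
|---|---|---|---|---|
| 96/48 | 40,000 | 0.985 | 5.66% | 5.08% |
| 40/20 (assumed) | 20,000 | 0.963 | 6.26% | 5.03% |

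A separate small run at 96/48 with 5% and 10% missingness at the two follow-ups gave an SE ratio of 0.984. It had only 300 replicates, too few for its rejection rates to be used.

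**6. How much is due to ML itself.** At N = 144 and p = 5, ML with a t reference gives 5.4% and REML with a normal reference 5.2%. About 0.4 percentage points come from ML and about 0.2 from a normal reference, which the article does not specify.

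**The case against.** The strongest reply is that the sentence is about missing data. It explains why participants with an absent outcome can stay in the analysis, and what it says about MAR is true. A reader might infer that the trial is locked into ML and that REML is excluded. The text does not go that far: it names ML, does not discuss REML, and the statistical analysis plan, where estimator and degrees of freedom are usually settled, is not shown. Silence on degrees of freedom is therefore no fault. What remains is that the article does name an estimator, and a literal reading leads to the slightly worse of two equally available choices.

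Three further objections are sound and limit the point.

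- Setting ML with a normal reference against REML with a t reference changes two things at once. Step 6 separates them.
- A reader might infer that secondary outcomes are analysed in small samples. No secondary outcome is given a reduced number, and the article plans no subgroup analyses. The carer-completed Zarit Burden Interview may have fewer contributors, because having a carer is not an eligibility criterion, but no figure is stated. The 60 used above is an illustration.
- The contrast between ML and REML applies to Gaussian models. For binary and count outcomes ML is the usual estimation, and the criticism does not carry over directly.

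**Conclusion.** The point holds as a minor correction of wording and method. If ML is used as written, the primary standard error is about 1.5–2.5% too small, and the nominal 5% test rejects about 5.3–5.8% of the time. The range covers four to seven mean parameters and a t or normal reference. The repeated-measures model with HY in three groups sits at the 1.5% end.

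A reader might conclude that the primary test materially fails its 5% level. The figures do not support that. The excess is under one percentage point, and only a p-value very close to 0.05 could change sides. The sample size and the estimand are unaffected, and the treatment estimate is essentially unchanged. A larger effect, about 5.8–7.1% at 60 contributors, rests wholly on an assumed number and concerns continuous secondary outcomes only.

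**What to change.** In the section on statistical methods for primary and secondary outcomes, state that linear mixed models for continuous outcomes are fitted by restricted maximum likelihood, with Kenward-Roger or Satterthwaite degrees of freedom for tests and intervals. Keep the MAR rationale, which holds equally for REML. Leave estimation of the binary and count models unchanged. If the statistical analysis plan already specifies REML, align this sentence with it.

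The cost is one changed sentence and a software option. Intervals become marginally wider, by about 1.5–2.5% at the planned size from the change of estimator, and by slightly more if a t replaces a normal reference. Recruitment, data collection and the sample size are untouched.
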